## Abstract

**Background:**

Heart failure (HF) is associated with decreased quality of life, high re-admission rate and poor prognosis. In particular, ischemic heart failure (IHF) has a worse prognosis than nonischemic HF. The use of traditional Chinese medicine (TCM) alongside Western medicine to treat HF has developed into an integrative treatment model in China. There have been small clinical trials and experimental studies to demonstrate the efficacy of TCM for treating HF; however, there is still a lack of high-quality trials. *Qishen Yiqi* dripping pills (QSYQ), a TCM drug, have been commonly used alongside standardized Western medicine to treat IHF. This paper describes the protocol for the clinical assessment of QSYQ in IHF patients.

**Method:**

A randomized, double-blind, multicenter, placebo-controlled trial will assess the efficacy and safety of QSYQ in the treatment of IHF. The trial is to enroll 640 IHF patients from 32 hospitals in China. Besides their standardized Western medicine, patients will be randomized to receive treatment of either QSYQ or placebo for 6 months and follow-up monitoring for at least a further 6 months. The primary outcome is increased exercise capacity of patients, which will be measured using the 6-minute walking test (6MWT). The secondary outcomes include composite endpoints: all-cause mortality, frequency of hospitalization or emergency due to cardiovascular events, brain natriuretic peptide levels, left ventricular ejection fraction, and cardiothoracic ratio will be documented, as well as scores on the New York Heart Association classification and Minnesota quality of life index, and information obtained from the four TCM diagnostic methods. Blood lipid tests will also be administered.

**Discussion:**

The integrative treatment model of TCM alongside Western medicine has developed into a treatment model in China. The rigorous design of the trial will assure an objective and scientific assessment of the efficacy and safety of QSYQ in the treatment of IHF.

**Trial registration:**

Clinical trials.gov number: NCT01555320

## Background

Heart failure (HF), as the endstage of various cardiac diseases, is associated with decreased quality of life, high re-admission rate, and poor prognosis. Some investigations showed that ischemic heart disease (IHD) was responsible for 70% of HF patients, while 40% of IHD patients died from HF [1-3]. Even with standardized treatment, the prognosis of patients with ischemic heart failure (IHF) is worse than in patients with nonischemic HF, especially for those with severe symptoms (New York Heart Association (NYHA) class IV) [4]. Their 1-year and 3-year mortality rates are 18% and 43%, respectively [4]. Nowadays, Western medicine treatment for HF is standardized around the world [5,6]; however, the integrative treatment of Western and traditional Chinese medicine (TCM) for HF is commonly used and developed as a treatment model in China [6].

*Qishen Yiqi* dripping pills (QSYQ, produced by Tasly Pharmaceutical Co. Ltd.), a patent drug made of active ingredients from *Huangqi*, *Danshen*, *Sanqi*, and *Jiangxiang,* has the effect of nourishing *Qi*, promoting blood circulation and relieving pain. The pills have been commonly used in TCM for the integrative treatment of patients with IHF who are also diagnosed with *Qi* deficiency and blood stasis syndrome [7,8]. Experimental researches have shown in animal models that QSYQ could inhibit platelet aggregation, prevent enlargement of end-diastolic diameter, improve left ventricular function, and slow down ventricular remodeling [9-14]. Some small-scale clinical studies on the drug demonstrated efficacies in improving left ventricular function, increasing exercise capacity and decreasing re-admission rate [15-19].

We would like to test the hypothesis that patients with IHF will benefit from TCM treatment QSYQ and evaluate its safety through a high-quality clinical trial.

### Objective

The objective of the trial is to assess the safety and clinical effects of QSYQ in improving the exercise capacity of IHF patients.

## Design

The CACT-IHF study is designed as a multicenter, randomized, double-blind, placebo-controlled trial, and will be conducted in 32 level-A hospitals in China. A total of 640 stable outpatients with IHF, who fulfill the inclusion and exclusion criteria, will be randomized into either a treatment group or a control group.

### Sample size

The sample size calculation was based on results from studies by Hutcheon *et al*. [20] and Mao *et al. *[21]. After 6 months of intervention, we assume that the distance walked in a 6-minute walking test (6MWT ) in the control group and treatment group will be up to 260 m and 288 m, respectively (that is, patients in the treatment group will walk an additional 28 m, *δ* = 115 m). Patients will be randomized in the ratio of 1:1 into two groups and each group requires at least 266 patients in order to produce positive results (one-tailed test, significant level *α* = 0.05, power (1 - *β*) = 0.80). Considering the loss of patients due to follow-up and a maximum dropout rate of less than or equal to 20%, the sample size was increased to 320. To calculate sample size, we used the equation:

$$n=\frac{2{\left(Z_{1-\alpha }+Z_{1-\beta }\right)}^{2}\delta^{2}}{{\left(\mu_{T}-\mu_{C}\right)}^{2}}$$

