### Statistical analysis

Statistical analysis for the trial will be performed by the Centre for Statistical Science, Peking University. Statistics software SAS 9.1 will be used for the data analysis. Intention-to-treat analysis, per-protocol analysis, and safety analysis will be conducted. Calculations for the outcomes will be based on a two-tailed test, except for the primary outcome, which will be a one-tailed test (level of significance *α* = 0.05). Besides the statistical comparison between baseline variables, the change in 6MWT result between baseline and the assessment 3 and 6 months during the treatment phase will be performed using analysis of covariance adjusted for baseline and treatment to improve the efficiency and power of the tests. Survival analysis will be conducted using Kaplan-Meier and Cox regression models. Statistical analysis on the missing data of the outcome measures will be adjusted using an estimating equation or statistical model in the final analysis. Sensitivity analyses will also be performed to assess the robustness of the data.

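### The 266 patients per group do not follow from the printed formula and its stated one-tailed inputs, which give 209; the mismatch is conservative, but sidedness, power and n must be made to agree

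*Protocol article*

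**What the plan says.** The Sample size section gives all the inputs of the calculation. The 6-month walking distances "in the control group and treatment group will be up to 260 m and 288 m, respectively", so that "patients in the treatment group will walk an additional 28 m". The value 115 m carries the symbol δ and stands in the formula where the standard deviation belongs. The test is described as "one-tailed test, significant level" 0.05, with "power (1 - *β*) = 0.80" and 1:1 allocation. The printed equation uses Z(1−α), the one-sided critical value. The result is that "each group requires at least 266 patients in order to produce positive results", raised to 320 per group for dropout of up to 20%.

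The Statistical analysis section repeats the sidedness: outcomes are tested two-tailed "except for the primary outcome, which will be a one-tailed test", again at alpha 0.05.

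**The concern.** Formula, inputs and result stand in one paragraph, so a reader can redo the calculation, and it does not come out at 266. The gap is too wide for rounding or a small-sample correction. At least one of the stated sidedness, power and sample size is therefore not what was used.

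This matters because sidedness sets the false-positive rate for a claim of benefit: 5% in the favourable direction under a one-tailed 0.05 test, 2.5% under a two-tailed 0.05 test. If the sizing and the planned test rest on different error rates, the stated 80% power is not the power of the planned test at the stated n.

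**Working it through.** **Inputs** (all from the Sample size section): difference 288 − 260 = 28 m; standard deviation 115 m; alpha 0.05 one-tailed; power 0.80; equal groups. The one-tailed 0.05 test is confirmed in the Statistical analysis section.

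**Step 1: the printed formula with the stated inputs.**

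n = 2 × (Z(1−α) + Z(1−β))² × SD² / difference²

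- Z(0.95) + Z(0.80) = 1.6449 + 0.8416 = 2.4865
- SD² / difference² = 13225 / 784 = 16.869
- n = 2 × 2.4865² × 16.869 = 208.6, so **209 per group**
- the t-based calculation gives 209.3, so 210

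The stated 266 is not reproduced. The excess is 266 − 209 = 57 per group, or 57/209 = 27% of the formula's own result.

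**Step 2: what would give 266?**

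| Change from the stated inputs | n per group |
|---|---|
| Two-tailed 0.05 (same as one-tailed 0.025), normal formula | 2 × (1.9600 + 0.8416)² × 16.869 = 264.8, so 265 |
| Two-tailed 0.05, t-based | 265.8, so 266 |
| One-tailed 0.05, power about 0.88 | close to 266 (264 at power 0.875, 269 at 0.88) |
| One-tailed 0.05, SD about 129.9 m | 266 |
| One-tailed 0.05, difference about 24.8 m | 266 |

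The two-tailed calculation is the only one in the table that keeps the stated difference, SD and power. It needs the t-based version to reach 266 exactly, and the article mentions no t-based calculation.

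**Step 3: power at the sizes in the plan**, from the normal approximation Φ(28 / (115 × √(2/n)) − Zcrit).

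| n per group | 28 / (115 × √(2/n)) | One-tailed 0.05 (Zcrit 1.6449) | Two-tailed 0.05 (Zcrit 1.9600) |
|---|---|---|---|
| 209 | 2.489 | 80.1% | 70.2% |
| 256 (320 × 0.80) | 2.755 | 86.6% | 78.7% |
| 266 | 2.808 | 87.8% | 80.2% |
| 320 | 3.080 | 92.4% | 86.9% |

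The noncentral-t values at 266 are 87.7% and 80.0%, so the choice of method does not matter here.

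**The case against.** The strongest reply is that the planned test is not in doubt. One-tailed 0.05 stands in the words of the Sample size section, in the Z(1−α) of its equation and in the Statistical analysis section, which deliberately sets the primary outcome apart from the two-tailed ones. Under that test the trial has more patients than its criteria need, even after the maximum planned loss, so no stated analysis is weakened. This stands, and it limits the point to a mismatch in the reported calculation.

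A reader might infer more, in two ways. The first is that the stated design is invalid or the trial underpowered. The documents show the opposite for the stated test: about 88% power at 266 and about 87% at 256, against a target of 80%. The second is that the trial was really designed as two-tailed and that the sidedness is misreported. That is the most plausible origin of 266, but it is an inference. The printed formula with 1.96 gives 265, not 266, and a different power, standard deviation or difference would also lead to 266.

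Two other defences fail. The words *at least* do not rescue the figure, because the minimum that the formula yields is 209. Nor is this a gap left by condensing a protocol into an article: formula, inputs and result are all printed and disagree, and an unseen analysis plan cannot make that formula yield 266.

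**Conclusion.** The point holds as an arithmetic inconsistency. The stated formula and inputs require 209 per group (210 t-based), not 266, so the stated one-tailed alpha 0.05, 80% power and 266 per group cannot all be true together. The error is conservative for the test that the plan says it will use, and it leaves that test's planned alpha untouched. A two-tailed 0.05 origin is likely but not shown.

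The direction would change only if the sponsor confirmed two-tailed sizing. Power would then be about 80% at 266 per group, but about 79% with the 256 left when 20% of 320 are lost.

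The result assumes that 115 m, labelled δ, is the common standard deviation, as its place in the formula implies. The label itself does not affect the numbers. The power figures are for the unadjusted comparison of two means on which the formula rests.

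**What to change.** Keep 320 per group. State which inputs and method produced 266, and correct the Sample size paragraph so that sidedness, power and n agree.

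- **If the one-tailed 0.05 test stands:** report 209 per group for 80% power, or keep 266 and report about 88% power. This is a wording correction in one paragraph, with no change to recruitment or analysis.
- **If the sponsor confirms that the trial was sized for a two-tailed 0.05 (one-tailed 0.025) test:** change the formula to Z(1−α/2), align the Statistical analysis section before unblinding, and state power of about 80% at 266 and about 79% at 256 per group after the maximum loss. This is more than wording, because it changes the primary decision rule in a trial that is already recruiting: a one-tailed p-value between 0.025 and 0.05 would no longer count as positive. It needs no extra patients if about 79% power after maximum loss is accepted and stated. Keeping 266 evaluable per group at 20% loss would take 266 / 0.80 = 332.5, so 333 per group.

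In either case, label 115 m as the standard deviation.

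### 320 per group does not keep the stated minimum of 266 at the stated 20% dropout: 256 remain, and the effect on power is small and depends on which test is planned

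*Protocol article*

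**What the plan says.** All of the figures are in the protocol article.

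- Sample size, requirement: "each group requires at least 266 patients in order to produce positive results".
- Sample size, test and power: "one-tailed test, significant level *α* = 0.05, power (1 - *β*) = 0.80". The assumed means are 260 m and 288 m, so that "patients in the treatment group will walk an additional 28 m". A value of 115 m is written as δ and stands in the printed equation where the standard deviation belongs.
- Sample size, allowance for loss: "a maximum dropout rate of less than or equal to 20%, the sample size was increased to 320".
- Design, total: "A total of 640 stable outpatients with IHF", which is 320 in each of two equal groups.
- Statistical analysis: tests are two-tailed "except for the primary outcome, which will be a one-tailed test", again at 0.05.

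The article does not show how it went from 266 to 320.

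**The concern.** An allowance for dropout exists so that the required number is still there after the loss. The required number is therefore divided by the fraction retained. Multiplying it by one plus the dropout rate gives too few, and the stated 320 looks like the result of that shortcut. If so, the plan promises at least 266 per group and tolerance of up to 20% loss, and 320 cannot deliver both.

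At stake is whether the statement about the primary outcome's sample size is true, and whether the 80% power target survives the worst dropout that the plan allows for. The second question cannot be answered without also asking which test the 266 belongs to.

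**Working it through.** **Inputs (all from Sample size, repeated in Design or Statistical analysis where noted).** Minimum 266 per group; dropout up to 20%; 320 per group (640 in total, Design); difference 28 m; standard deviation 115 m; 1:1 allocation; one-tailed α = 0.05 (also in Statistical analysis); target power 0.80.

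**1. Reproduce 320.**
- 266 × (1 + 0.20) = 319.2, rounded up to 320. This matches.
- 266 / (1 − 0.20) = 332.5, rounded up to 333. This does not match.

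Multiplication by 1.2 is therefore the likely route. It is an inference from the arithmetic.

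**2. Test 320 against the stated claim.** This step does not depend on how 320 was obtained.
- 320 × 0.80 = 256, which is 266 − 256 = 10 short per group.
- Largest dropout that keeps 266: 1 − 266/320 = 54/320 = 16.9%.
- Number that would keep 266 at 20% dropout: 333 per group, 666 in total, which is 13 more per group and 26 more in total.

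**3. Reproduce 266.** The printed formula is n = 2(Z₁₋α + Z₁₋β)² × 115² / 28².
- One-tailed 0.05, as stated: 2 × (1.645 + 0.842)² × 13225 / 784 = 208.6, so 209. This does not match 266.
- Two-tailed 0.05: 2 × (1.960 + 0.842)² × 13225 / 784 = 264.8, so 265. With the t distribution in place of the normal, power is 79.9% at 265 and 80.0% at 266, so 266 is the smallest group size that reaches 80%. This matches.

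The stated 266 therefore fits a two-tailed test, although both sections specify a one-tailed one.

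**4. Power with and without the shortfall.** Noncentral t, with noncentrality 28 / (115 × √(2/n)), no baseline adjustment:

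| n per group | One-tailed 0.05 (stated) | Two-tailed 0.05 (reproduces 266) |
|---|---|---|
| 266 | 87.7% | 80.0% |
| 256 | 86.6% | 78.5% |

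The loss is about 1.1 points one-tailed and 1.5 points two-tailed.

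**5. The allowance if the stated test and printed formula are taken at face value.** 209 / 0.80 = 261.25, so 262 per group. Then 320 per group would tolerate 1 − 209/320 = 34.7% dropout.

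**The case against.** The strongest reply accepts the arithmetic and disputes its importance. The plan fixes a one-tailed primary test in two places. Under that test the printed formula needs 209 per group, or 262 after a proper 20% allowance, so 320 is more than enough and 256 patients still give about 86.6% power. On this view the larger defect is the 266, and the dropout slip has no adverse effect on power once that is corrected.

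This stands as far as power goes. A reader might infer from the shortfall that the trial misses its 80% target at 20% dropout. The article does not support that: the figure below 80% appears only under a two-tailed test, which the plan does not specify for the primary outcome. The reply does not rescue the dropout sentence itself, because the article states 266 as the minimum, not 209, and presents 320 as that number after the allowance for loss. A second discrepancy that happens to offset the first does not make the sentence true.

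Two further points limit the effect.

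- Statistical analysis plans covariance analysis adjusted for baseline. If residual variance scales as 1 − r², the loss from 266 to 256 is offset once r² = 1 − 256/266 = 0.038, that is r of about 0.19. The article gives no correlation, so this is only a break-even value.
- Missing outcomes are to be handled by a model, and a walking test is also scheduled at 3 months, so some patients who drop out may still contribute. Treating 256 complete cases as all the information is the worst case.

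It may also be said that 20% is only a ceiling. But the allowance is stated to cover that ceiling, and it fails for any dropout above 16.9% and up to 20%.

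**Conclusion.** The point holds as an internal inconsistency in the Sample size section: 266 as a minimum, 20% as the tolerated dropout and 320 per group are incompatible. The gap is 10 patients per group after loss, or 13 per group at randomization. This part rests on nothing but the article's own numbers. Only the explanation, multiplication by 1.2, is inferred.

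The consequence is small. At the stated maximum dropout, power is about 86.6% for the planned one-tailed test, above the target, and about 78.5% on the two-tailed basis that yields 266. Both figures assume a 28 m difference, a standard deviation of 115 m, complete cases only and no gain from baseline adjustment. The documents do not support calling the trial underpowered under its stated test. Nor is the total of 640 wrong in itself; what is wrong is the claim about what it covers.

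**What to change.** Keep 640 patients and correct the text, in this order.

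1. Reconcile 266 with the stated test. Either the sample size section acknowledges that 266 comes from a two-tailed 0.05 calculation, or it gives the number that the printed one-tailed formula produces (209 per group, 262 after dividing by 0.8). The sidedness in the Sample size and Statistical analysis sections must then agree with the choice.
2. Restate the dropout sentence, for example: 320 per group leaves 256 at 20% dropout; 266 are retained only up to 16.9% dropout.
3. Add the power at 256 per group for the test actually planned: about 86.6% if one-tailed 0.05, about 78.5% if two-tailed 0.05, each before any gain from baseline adjustment. A two-tailed power figure should not be put into a plan that still specifies a one-tailed test.

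The cost is wording only: no additional patients and no change to the conduct of the trial. The stated dropout tolerance becomes slightly less favourable if 266 is kept as the requirement.

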### Inclusion criteria

• Age 40 to 79 years.

• Patients with IHF:

◦ Left ventricular ejection fraction ≤45%, as measured by echocardiography in modified Simpson method.

◦ History of myocardial infarction with or without percutaneous coronary intervention or coronary artery bypass grafting.

◦ Coronary angiography or coronary computed tomography angiography shows ≥50% stenosis in at least one main coronary artery with or without revascularization, which the researcher thinks is closely related to HF.

◦ With or without dyspnea, fatigue and fluid retention (edema), and so on.

• History of HF or present with HF symptoms for at least 3 months.

• NYHA Class II to IV.

• Submitted informed consent.

### Exclusion criteria

• Acute HF or acute exacerbation of chronic HF.

• Patients with one of the following diseases:

◦ Acute coronary syndrome within 30 days.

◦ Revascularization therapy within 6 months.

◦ Uncontrolled hypertension with systolic pressure ≥180 mmHg or diastolic pressure ≥110 mmHg.

◦ Second-degree type 2 or worse sinoatrial or atrioventricular block without implantation of pacemaker or uncontrolled malignant cardiac arrhythmia.

◦ Dilated cardiomyopathy.

◦ Hypertrophic obstructive cardiomyopathy.

◦ Myocarditis.

◦ Pulmonary artery embolism.

◦ Severe valvular heart disease

◦ Pulmonary heart disease.

◦ Stroke within 6 months.

• Cardiac resynchronization therapy.

• Applied diuretics, cardiotonic agents, or vasodilators intravenously within 7 days.

• Severe endocrine diseases, such as hyperthyroidism.

• History of malignant tumor.

• Hemoglobin ≤ 9 g/dl.

• Alanine aminotransferase more than twice the upper limit of normal.

• Serum creatinine >265 μmol/l.

• Mental disorder.

• Pregnant, planning for pregnancy or breastfeeding.

• Suspicious or definite allergy to intervention drugs.

• Participated in other trials within 2 months.

• Unable to walk autonomously, owing to physical disabilities.

### Randomization procedure

Included patients will be randomly assigned to a treatment or control group in the ratio of 1:1. Stratification will be performed on NYHA classification, enrolling hospitals, and revascularization methods. Eligible patients will be randomized by IWRS/IVRS software (ClinicalSoft Co. Ltd.) into the intervention arms. The identification number and randomization code generated are unique to each patient and correspond to the coded boxes of either QSYQ or a placebo matched in appearance, color, and shape to the drug. The flavor of the drug and placebo are also similar. Blinding will be maintained amongst the investigators and patients.

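### The stated primary ANCOVA leaves out all three factors used to stratify randomization; adding them brings a small gain for a change of wording only

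*Protocol article*

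**What the plan says.** All references are to the protocol article.

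- Design: the trial "will be conducted in 32 level-A hospitals in China", and "A total of 640 stable outpatients with IHF, who fulfill the inclusion and exclusion criteria, will be randomized".
- Randomization procedure, on the allocation ratio: "Included patients will be randomly assigned to a treatment or control group in the ratio of 1:1". On the strata, the same section says that "Stratification will be performed on NYHA classification, enrolling hospitals, and revascularization methods". On the system used, it says that "Eligible patients will be randomized by IWRS/IVRS software". The article does not give the levels of NYHA class or revascularization used as strata, whether the factors are fully crossed, the block size, or whether the system uses permuted blocks or a dynamic method.
- Inclusion criteria: "NYHA Class II to IV"; and "History of myocardial infarction with or without percutaneous coronary intervention or coronary artery bypass grafting".
- Statistical analysis: the change in 6MWT at 3 and 6 months is tested by "analysis of covariance adjusted for baseline and treatment". Kaplan-Meier and Cox models are planned for the survival analysis, without a list of covariates.

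**The concern.** Stratifying on a factor makes the arms more alike on it. A model that omits the factor still counts its contribution as noise, so the reported standard error tends to exceed the true one and the test is a little conservative. Where stratification balances less well, for example because the cells are sparse, the omitted factor remains as uncorrected chance imbalance. Either way the primary model forgoes something that the design has already paid for.

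NYHA class should matter both for walking distance and for the composite of death and cardiovascular hospitalization or emergency; the Background singles out class IV for its poor prognosis. Three factors, one of them with 32 levels, also raise the question of how much balance on NYHA class and revascularization the scheme can deliver.

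**Working it through.** **Inputs from the article.** 640 patients (320 per group), 32 hospitals, 1:1 allocation, NYHA II to IV. The Sample size section gives 266 evaluable patients per group and 115 m, printed as δ but used in the formula as the standard deviation. (266 fits a two-sided calculation, which gives 265; the one-tailed formula as printed gives 209. That is a separate matter.) The article states no number of strata, so there is no such figure to reproduce.

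**Assumptions.** Three NYHA levels; two (yes/no) or three (none/PCI/CABG) revascularization levels; full crossing; permuted blocks.

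**1. Cells.**
- 32 × 3 × 2 = 192 cells; 640/192 = 3.3 patients each.
- 32 × 3 × 3 = 288 cells; 640/288 = 2.2 patients each.
- A hospital averages 640/32 = 20 patients over 6-9 cells.
- If both factors had two levels: 32 × 2 × 2 = 128 cells; 640/128 = 5.0 each.

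**2. Balance by block size.** Simulation of blocks within crossed cells, 600 trials per scenario, several class mixes. The table gives the variance of the arm difference in patient numbers within a class, as a share of that under simple randomization. The small class is an assumed 10% in NYHA IV or 15% in one revascularization group.

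| Block size | Larger classes | Small class |
|---|---|---|
| 2 | 11-24% | 29-58% |
| 4 | 17-47% | 55-90% |
| 6 | 23-71% | 61-82% |
| 8 | 45-72% | 84-95% (blocks 8-10) |
| 10 | 58-83% | as above |

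Without hospital in the crossing (6-9 cells, blocks of 4-6) the share is 1-5%.

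**3. One worked case.** Blocks of 4, NYHA 50/40/10%, revascularization 45/45/10%, equal hospitals. About 209 cells are used and about 177 end on an incomplete block. Under simple randomization the SD of the arm difference is √n.
- NYHA II (n = 320): SD 8.5; share 8.5²/320 = 23%.
- NYHA III (n = 256): SD 8.4; share 8.4²/256 = 28%.
- NYHA IV (n = 64): SD 6.6; share 6.6²/64 = 68%.

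Minimisation on the same three factors gives SDs of 1.9, 1.9 and 1.8.

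**4. What this means for the primary outcome.**
- Standard error without adjustment: 115 × √(2/266) = 9.97 m.
- An SD of 6.6 patients in NYHA IV is 6.6/320 = 2.06 percentage points of class share between the arms.
- Suppose NYHA IV differs from the rest by 30-100 m after allowing for baseline 6MWT (assumed). The imbalance then moves the treatment difference by an SD of 0.0206 × 30 = 0.6 m to 0.0206 × 100 = 2.1 m. As a share of the variance this is (0.62/9.97)² = 0.4% to (2.06/9.97)² = 4.3%.
- Precision available from fitting this factor: it contributes 0.1 × 0.9 × 30² = 81 m² to 0.1 × 0.9 × 100² = 900 m², which is 0.6% to 6.8% of 115² = 13,225 m². Removing it takes the standard error from 9.97 m to 9.97 × √(1 − 0.006) = 9.94 m, or to 9.97 × √(1 − 0.068) = 9.62 m.

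The 115 m is used because the article gives no correlation between baseline and follow-up distance. With a smaller residual SD the same 30-100 m would be a larger share.

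**5. Fitting the cells as randomised.** With 2 × 266 = 532 evaluable patients there would be 532/192 = 2.8 or 532/288 = 1.8 per cell, too few to fit. Main effects need 2 parameters for NYHA class, 1-2 for revascularization and one variance component for hospital.

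**The case against.** Two stronger readings are tempting.

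*The balance that stratification is meant to give is largely lost.* The article does not support this. It states neither full crossing nor permuted blocks, and central IWRS software may well run minimisation, which balances the three margins however many cells there are. These details are commonly left to the full protocol. Even with crossed blocks of 2-4, the larger classes keep about half to nine-tenths of the variance reduction. Balance close to coin tossing arises only in a small class at blocks of 4 or more, or with large blocks; in a small class at blocks of 2, 42-71% of the reduction is still kept.

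*The allocation scheme should be changed.* This does not follow either. Randomization remains valid, and chance imbalance is not bias. Precision lost through overall imbalance is negligible: with an SD of 13.9 patients, (13.9/640)² = 0.05%. Dropping hospital from the strata would raise the mean absolute difference per hospital from 1.95 to 3.49 patients, about that of simple randomization (3.55). Recruitment has run since March 2012 and the codes are tied to coded drug boxes, so a switch would leave two schemes in one trial.

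It can also be said that baseline 6MWT already carries much of what NYHA class predicts about walking distance, that Cox regression and sensitivity analyses are planned, and that a fuller plan may list covariates. The first is true and is why the gain is small. The others do not alter the primary model, whose adjustment terms the article states without any stratification factor. The unlisted Cox covariates are no fault in an article.

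**Conclusion.** The point holds for the analysis: the stated primary model ignores all three stratification factors. The result stays valid but is slightly conservative and less precise than the design allows, and imbalance on NYHA class or revascularization is only partly corrected through baseline 6MWT.

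The size is small. For an NYHA IV class of 10% that differs by 30-100 m beyond baseline, fitting the factor lowers the standard error by about 0.3-3.5%; the other factors could add to this by an amount that the article does not allow one to compute. The Kaplan-Meier comparison gets no help from baseline 6MWT, so there the Cox covariates matter more.

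The sparse cells (192-288, about 2-3 patients each) are a conditional point. It rests on the assumed levels, full crossing and permuted blocks, varies widely with block size, and disappears under minimisation.

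**What to change.** - In Statistical analysis, replace the stated adjustment by an ANCOVA with baseline 6MWT, treatment, NYHA class and revascularization method as main effects, and hospital as a random effect.
- Include NYHA class and revascularization method in the Cox model.
- Do not fit the crossed cells.
- Add one sentence giving the allocation algorithm, the factor levels and, if blocks are used, that they are; if the system minimises, this settles the balance question.

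The cost is analysis wording, to be fixed before unblinding. It needs no extra patients, visits or staff, and is sound whichever algorithm the IWRS runs. No change to the allocation scheme during recruitment is required.
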